## 2. List of Abbreviations

|       |                                                                                         |
|-------|-----------------------------------------------------------------------------------------|
| CMC   | Cortico-muscular coherence                                                              |
| CTT   | Color Trail Test                                                                        |
| CoM   | Centre of Mass                                                                          |
| EEG   | Electroencephalography                                                                  |
| EMG   | Electromyography                                                                        |
| EQ-5D | Euro-Qol (general and validated questionnaire to assess health-related quality of life) |
| FCI   | Groll Functional Comorbidity Index                                                      |
| FES-I | Falls Efficacy Scale International                                                      |
| FI    | Frailty Index                                                                           |
| FACIT | Functional Assessment of Chronic Illness Therapy                                        |
| FOG   | Freezing of gait                                                                        |
| H&Y   | Hoehn & Yahr Staging of Parkinson's disease                                             |
| HC    | Healthy controls                                                                        |
| MoCA  | Montreal Cognitive Assessment                                                           |
| PD    | Parkinson's disease                                                                     |
| PwPD  | Patients with Parkinson's disease                                                       |
| PI    | Principal Investigator                                                                  |
| SDTT  | Speed-dependent treadmill training                                                      |
| TUG   | Timed Up and Go                                                                         |
| UPDRS | Unified Parkinson's Disease Rating Scale                                                |
| VAS   | Visual Analogue Scale                                                                   |
| WP    | Work Package                                                                            |
| 2MWT  | Two-minute walking test                                                                 |

## i. Trial Summary

|                                    |                                                                                                                                                                                                                                                                                                                           |                  |
|------------------------------------|---------------------------------------------------------------------------------------------------------------------------------------------------------------------------------------------------------------------------------------------------------------------------------------------------------------------------|------------------|
| Trial Title                        | Steps against the burden of Parkinson's Disease                                                                                                                                                                                                                                                                           |                  |
| Internal ref. no. (or short title) | StepuP                                                                                                                                                                                                                                                                                                                    |                  |
| Trial Design                       | Multicentre non-pharmacological randomized controlled trial                                                                                                                                                                                                                                                               |                  |
| Participants                       | Patients with Parkinson's disease (PwPD) recruiting at four different clinical centres and Healthy Controls (HC) recruiting at Amsterdam                                                                                                                                                                                  |                  |
| Intervention                       | Speed-dependent treadmill training (i.e, treadmill walking at alternating blocks of different percentages of comfortable walking speed) for 12 sessions with perturbations (sessions between T0 and T1).                                                                                                                  |                  |
| Control                            | Speed-dependent treadmill training without perturbations (12 sessions between T0 and T1).                                                                                                                                                                                                                                 |                  |
| Maintenance                        | Both groups receive home-based speed-dependent walk training using a phone app for maintenance of treadmill training benefits between the T1 post-training and T2 follow-up assessments. Includes goal setting towards World Health Organisation physical activity recommendations.                                       |                  |
| Outcomes                           | Measures                                                                                                                                                                                                                                                                                                           | Domain    |
|                                    | Primary outcome
Gait speed (m/sec)                                                                                                                                                                                                                                                                                     | Gait performance |
|                                    | Step width
Step width variability
Stride time
Stride time variability
Stride length variability
Stride length                                                                                                                                                                                              | Walking          |
|                                    | Disease severity (MDS-UPDRS III)
Hoehn & Yahr (H&Y)
Cognitive function (MoCA & TMT)
Depressive symptoms (BDI II)
Fear of falling (Short FES-I)
Health-related quality of life (EQ-5D)
Fatigue (FACIT)
Physical capacity (2MWT, TUG, MiniBESTest, Grip strength)
Pain and Walking confidence (VAS) | Clinical         |

|                      |                                                                                                                                                                                                                                                                                                                                                                                                                                                                                  |                                        |
|----------------------|----------------------------------------------------------------------------------------------------------------------------------------------------------------------------------------------------------------------------------------------------------------------------------------------------------------------------------------------------------------------------------------------------------------------------------------------------------------------------------|----------------------------------------|
|                      | Comorbidities (FCI)                                                                                                                                                                                                                                                                                                                                                                                                                                                              |                                        |
|                      | Local divergence exponent
Foot placement model (multiple linear regression) : 
 
- Relative explained variance (<math>R^2</math>)
 
- Standard deviation of residual (i.e. foot placement error)
 
- Regression coefficients
 
                                                                                                                                                                                     | Kinematics                             |
|                      | Beta-band Power in motor areas
Cortico-muscular coherence                                                                                                                                                                                                                                                                                                                                                                                                                     | Neurophysiological                     |
|                      | Steps per day
Amount and length of uninterrupted walk durations
Stride time variability
Symmetry                                                                                                                                                                                                                                                                                                                                                                        | Home assessment                        |
|                      | Adverse events
Falls and injuries
Mobility
Fatigue
Exercise Adherence
Health services use                                                                                                                                                                                                                                                                                                                                                                         | Weekly Calendars and Safety Monitoring |
|                      | End-user engagement questionnaires at T1 (regarding treadmill training) and T2 (regarding home-based maintenance walking): 
 
- System usability
 
- Physical Activity Enjoyment
 
- Exercise Self Efficacy
 
- Barriers and Enablers to long term use
 
 Qualitative interviews using open questions to elicit greater understanding of the individual experiences and barriers and enablers to long term use. | Engagement and Process                 |
| Planned Trial Period | 24 months                                                                                                                                                                                                                                                                                                                                                                                                                                                                        |                                        |
| Planned Sample Size  | 126 participants with PD
21 healthy controls (Amsterdam)                                                                                                                                                                                                                                                                                                                                                                                                                      |                                        |

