## 5. The StepuP trial design

### i. Study design

StepuP is a multicenter non-pharmacological randomized controlled trial (RCT) conducted at four clinical centers: Christian-Albrechts-Universität zu Kiel (Kiel), Tel Aviv Sourasky Medical Center (Tel Aviv), University of New South Wales (Sydney), IRCCS Istituto delle Scienze Neurologiche di Bologna (Bologna). 42 PwPD will be enrolled and will be randomized into an intervention group (IG) and a control group (CG) at the clinical sites in Kiel and Sydney. 21 PwPD will be enrolled in Tel Aviv and Bologna and randomized as well into an IG and CG. All Participants will receive a 2-6 week speed-dependent treadmill training (SDTT) aimed at improving gait. Subjects in the IG will receive the same STDD with additional perturbations (SDTT+). Baseline (To) and follow-up (T1 & T2) visits include descriptive, clinical, kinematic and neurophysiological assessment. A 7-day home monitoring with digital sensors will be performed before To and after T2. In Sydney half of the patients in the CG and half of the patients in the IG will have also a second baseline measurement before receiving the SDTT.

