### ii. Specific Workpackages

The work within the trial will be broken down into specific work packages (WP), into which the sites mentioned above and other two other sites (Vrije Universiteit Amsterdam, [name]. [name], [[contact]](mailto:[contact]) (Amsterdam) and Swiss Federal Institute of Technology, [name], [[contact]](mailto:[contact]) (Zürich)) contribute. The WP are explained in more detail in the following. Please note that only the clinical centers (Bologna, Kiel, Sydney and Tel Aviv) conduct active recruitment and training, and therefore seek for ethical approval. Figure 1 shows the interaction between WP.

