### **iii. Participants**

Participants will be enrolled within the study across the four clinical centers on the basis of the following inclusion and exclusion criteria (Table 1):

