## **v. Case-control study (1b)**

### **Population:**

21 (min. 17 for analysis) PD patients (To) randomly selected from total sample

21 (min. 17 for analysis) healthy controls age- and sex-matched to PD group

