### **Analysis technique:**

Initially, independent t-tests and for EEG data cluster-based permutation tests time locked to the gait cycle will be used to compare patients to controls. The presence of and direction of differences between groups will facilitate interpretation for any effects found in analyses 2a - 2c. For this no corrections for multiple comparisons will be made. However, to present overall differences between groups we will reduce dimensionality of the set of primary and secondary clinical outcomes by means of PCA and use stepwise logistic regression on PC-scores to assess between group differences. For feedback control variables and neural correlates we will separately correct for multiple comparisons.

vi. SDTT vs. SDTT+ (2a)

Added value of additional component (SDTT+) to Speed Dependent Treadmill Training (SD Analysis technique.

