### **Analysis technique:**

We will correlate changes in primary outcomes (e.g., walking speed) with changes in behavioural (foot placement coordination) and neural (EEG beta band power, cortico-muscular coherence) outcomes. Multilevel models will be used, to account for data collected at different sites. For outcomes T2-To, potential predictors of clinical outcomes will include independent variables with a time lag (T1-To) and without time lag (T2-To).

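### Analysis 1b takes all healthy controls from Amsterdam and all patients from four other centres, so disease and laboratory differences cannot be separated; the protocol also disagrees with itself on whether Amsterdam recruits

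*Protocol*

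**What the plan says.** The Trial Summary (section 2.i) gives the participants as "Patients with Parkinson's disease (PwPD) recruiting at four different clinical centres and Healthy Controls (HC) recruiting at Amsterdam", and its sample-size row repeats the location: "21 healthy controls (Amsterdam". Section 5.i says "StepuP is a multicenter non-pharmacological randomized controlled trial (RCT) conducted at four clinical centers", namely Kiel, Tel Aviv, Sydney and Bologna. Table 2 allocates all 126 patients to those four and none to Amsterdam.

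Section 6.v (analysis 1b) defines the patient group as "21 (min. 17 for analysis) PD patients (To) randomly selected from total sample". The control group has the same size and is matched on age and sex only. The comparison uses independent t-tests, cluster-based permutation tests for EEG, and then principal components with stepwise logistic regression. No centre or laboratory term appears. On the use of the results, the section says "The presence of and direction of differences between groups will facilitate interpretation for any effects found in analyses 2a - 2c".

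Elsewhere the protocol does allow for centre. Analysis 2a nests participants within centre, and for 3b section 6.viii states "Multilevel models will be used, to account for data collected at different sites".

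On recruitment, section 5.ii names Amsterdam as one of two further contributing sites and says "only the clinical centers (Bologna, Kiel, Sydney and Tel Aviv) conduct active recruitment and training, and therefore seek for ethical approval". Section 5.iii adds: "Participants will be enrolled within the study across the four clinical centers".

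**The concern.** A patient-control contrast is interpretable as disease only if patients and controls could have been measured under the same conditions. Here every control comes from one centre and every patient from another. A systematic difference in treadmill walking, motion capture, EEG or EMG acquisition, or operators between Amsterdam and the clinical centres would appear in 1b as a feature of Parkinson's disease. Matching on age and sex does nothing about this.

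Analysis 1b has some weight in the argument. Section 6.ii explains that the placebo comparison was dropped and that the patient-control comparison helps to interpret change in the patients. If the presence or direction of a 1b difference is partly a laboratory effect, that guide is unreliable. The exposure is probably greatest for EEG power, coherence, foot-placement control and treadmill kinematics.

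The second issue is plain wording. The summary has Amsterdam recruiting 21 people, while section 5.ii excludes Amsterdam from recruitment and ties the seeking of ethical approval to recruitment.

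**Working it through.** **The plan's own figure.** Section 6.v has no sample-size calculation. Its 17 and 21 match section 6.i: difference 0.08 m/sec, SD 0.08, so a standardised effect of 0.08/0.08 = 1.0, alpha 0.05 (two-sided assumed), power 0.80. The exact t-test gives power 0.781 at 16 per group and 0.807 at 17, so 17 reproduces. The dropout step in the text is 17 × 1.2 = 20.4. None of this allows for a laboratory effect.

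**Can site be adjusted for?** Take five site indicators (four clinical centres and Amsterdam) plus an indicator for PD. The PD column equals the sum of the four clinical-centre columns, so the matrix has 6 columns and rank 5, and the PD effect cannot be estimated once site is in the model. If controls were measured at the same four centres as the patients, four site indicators plus PD give 5 columns and rank 5, and the effect becomes estimable within site.

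**Size of a chance offset.** The protocol gives no between-site variance, so a range is assumed. Let the share s be the between-site fraction of a total outcome variance of 1. Patients are drawn in proportion to 42, 42, 21 and 21 of 126, that is 1/3, 1/3, 1/6 and 1/6. The variance of the spurious patient-control offset is

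s × (1 + 2 × (1/3)² + 2 × (1/6)²) = s × (1 + 2/9 + 2/36) = 1.28 s.

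Rejection rates come from 40,000 simulated studies per value of s, with no disease effect, 21 versus 21, and a two-sided t-test at 5%:

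| Assumed s | SD of offset (outcome SDs) | Rejection rate |
|---|---|---|
| 0.02 | 0.16 | 8% |
| 0.05 | 0.25 | 13% |
| 0.10 | 0.36 | 20% |
| 0.20 | 0.51 | 32% to 33% over repeated runs |

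**Fixed offset instead.** If Amsterdam differs from the rest by a constant, the noncentral t distribution gives these rejection rates with no disease effect:

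| Offset (SD) | 21 per group | 17 per group |
|---|---|---|
| 0.10 | 6.2% | 5.9% |
| 0.25 | 12.4% | 10.9% |
| 0.50 | 35.3% | 29.3% |
| 0.75 | 66.0% | 56.4% |

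Recruiting more people at the same centres does not remove the offset. It only makes the test more sensitive to it, as the comparison of 17 with 21 shows.

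**Recruitment wording.** The Trial Summary has controls recruited in Amsterdam. Section 5.ii confines active recruitment, and with it the seeking of approval, to Bologna, Kiel, Sydney and Tel Aviv. Section 5.iii confines enrolment to the four clinical centres. These statements cannot all be true of the controls.

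**The case against.** Several points on the other side are sound.

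- *Measurement site.* The text says controls are recruited in Amsterdam; it does not say they are measured there. The aliasing depends on that reading, although nothing in the protocol suggests another.
- *Equipment.* A reader might infer that Amsterdam uses different hardware, because the training perturbations differ between clinical centres. The documents do not support that: they never describe Amsterdam's equipment, and the 1b outcomes come from assessments without perturbation. The point is that an offset cannot be ruled out or estimated, not that one is known to exist.
- *Mitigation.* Amsterdam leads the work package that standardises data collection (section 5.ii.B), and electrode positions are projected to a shared coordinate system (section 5.vii). Both may shrink an offset. Neither makes it estimable, and no bridging participants or cross-laboratory calibration are described.
- *Role of 1b.* It is supportive and has no decision rule. A reader might infer that the trial's main results are compromised. They are not: the randomised comparisons and the pooled mechanism analyses use no control data.
- *Sign reversal.* A reader might infer that a laboratory offset would reverse the reading of a training effect. The calculations show false positives under no disease effect. Reversal would need an offset that opposes and exceeds the true difference, and nothing in the documents establishes that.
- *Ethics.* A reader might infer that controls would be recruited without approval. Section 7.i says the protocol goes to the local ethical boards and does not limit this to four centres. What stands is a contradiction in wording, not evidence of missing approval.

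**Conclusion.** The point holds for analysis 1b. On the natural reading that controls are measured where they are recruited, PD status and laboratory are fully aliased, and the planned tests estimate the two together. This cannot be repaired by modelling after the data are collected. The size is unknown: false-positive rates of about 8% to 33% correspond to assumed between-site shares of 0.02 to 0.20, so the problem is minor at the low end and substantial at the high end. It probably matters least for 20-m overground gait speed, which depends least on laboratory equipment, although that outcome is still confounded with site. The consequence is limited to how 1b may be used to interpret 2a to 2c. The contradiction between the Trial Summary and sections 5.ii and 5.iii stands on the text alone and needs no assumption.

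**What to change.** 1. In section 6.v, state that 1b differences in treadmill kinematics, foot-placement control, EEG power and EEG-EMG coherence combine disease and laboratory, and that their presence or direction alone will not be used to interpret 2a to 2c. The 20-m gait speed may still be used, with a site caveat. The cost is wording and weaker claims from 1b.

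2. As a sensitivity analysis only, estimate the between-site variance from the four clinical centres at T0 and add about 1.28 times that variance to the *squared* standard error of each patient-control difference. For an outcome with SD 1 and 21 per group, the squared standard error is about 2/21 = 0.095. With s = 0.10 it becomes 0.095 + 0.128 = 0.223, so the standard error rises from 0.31 to 0.47, about one and a half times. Report that four centres give only 3 degrees of freedom and that their spread includes case mix as well as laboratory, so the result indicates plausible size and does not correct the offset. The cost is wider intervals.

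3. Reconcile sections 5.ii and 5.iii with the Trial Summary so that every centre recruiting controls is named and covered by ethical approval, and say where controls are measured. The cost is a short text change.

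4. Optional, if controls are not yet recruited: measure some or all of the same 21 at the clinical centres so that PD status can be compared within site. In proportion to enrolment, all 21 would be about 7, 7, 4 and 3. This needs no more controls, but it adds ethics wording and about 3 to 7 single visits per centre. Whether that is worthwhile for a supportive analysis is open to debate.
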